## Methods/design

A community-based randomized controlled trial that is pragmatic in nature, following a parallel-group design will be conducted. Patients with T2D (*N* = 200) will be recruited from across 12 pharmacy locations in the province of British Columbia, Canada. The pharmacists will use a secure password-protected website maintained by the University of British Columbia (UBC) Centre for Health Evaluation and Outcome Sciences (CHEOS) to implement the random allocation sequence. The secure website provides allocation concealment until the interventions are assigned. The allocation sequence generated was by a researcher from CHEOS using PROC PLAN in SAS 6.4 software. Participants will be stratified by site (pharmacy) and glucose-lowering medications (two or fewer, three or more (or taking exogenous insulin)) and randomized in a 1:1 allocation ratio using permuted block sizes, to either the therapeutic nutrition group or the treatment-as-usual (TAU) group. Due to the nature of the interventions and the involvement required of the pharmacists, they cannot be blinded to final treatment allocations of the participants. The protocol was approved by the University of British Columbia Clinical Research Ethics Board (H16–01539) and the trial was registered on ClinicalTrials.gov (NCT03181165) on 8 June 2017. A flow diagram of the trial is presented in Fig. 1. Additional file 3 contains the SPIRIT 2013 Checklist.

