### Secondary outcomes

The secondary outcomes are:
Hemoglobin A1C (%)Percentage dose reduction in glucose-lowering medications (change in daily dose)Body mass index (BMI) (kilograms/meters squared) and weight reduction (kilograms)Waist circumference (centimeters)Body fat percentage (%)Health-related quality of life (SF-20)Blood lipid profile (total, high-density lipoprotein (HDL) and low-density lipoprotein (LDL) cholesterol, triglycerides), liver function tests (alanine aminotransferase (ALT), aspartate aminotransferase (AST), gamma-glutamyl transpeptidase (GGT)), fasting plasma glucose, pro-insulin, insulin, and C-peptideBlood pressure (millimeters of mercury)Percentage dose reduction in blood pressure-lowering medications (change in daily dose)

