### Statistical analysis

Data will be analyzed on an intention-to-treat basis at the 12-week (post-testing) timepoint. The primary outcome measure is binary - using or not using glucose-lowering medication at 12 weeks - and data will be analyzed by logistic regression, with the stratified allocation factors included as fixed effects together with trial arm and sex. We will derive the odds ratio for use of glucose-lowering medication, and odds will be converted to predicted probabilities (risk differences). Participants who fail to complete the intervention or are lost to follow up from the Pharm-TCR group will be retained in the analyses and will be considered as not achieving the primary outcome. The secondary outcome measures of anthropometrics, blood pressure, medication dose changes, quality of life, and all blood measures will be analyzed using constrained baseline longitudinal data analysis via a linear mixed model [25]. This approach provides a principled method for addressing missing data, including missing baseline data as baseline values are part of the response vector in this model. In addition, study site will be included as a random effect in the linear mixed models to account for site variability in the outcome measures [26]. Model specification will be examined by visual inspection of residuals plots, with appropriate data transformations used if indicated. For the primary endpoint we shall report the odds ratios and predicted probabilities (risk differences) with 95% confidence intervals. Secondary continuous outcomes will be reported as mean differences with 95% confidence intervals. Whenever possible, data analysis will be performed blinded to the allocations.

It is not anticipated that any participants in the TAU group will discontinue glucose-lowering medications; however, to be conservative, the sample size was calculated based on an expected proportion of medication use of 80% in the TAU group and a 20% difference in the proportion of participants on glucose-lowering medications at 12 weeks in the Pharm-TCR group. A sample size of 100 per group provides 80% power to detect a 20% difference in the proportion of patients on glucose-lowering medications, accounting for 20% attrition with a two-sided *P* value of 0.05 (PASS 14 Power Analysis and Sample Size Software, 2015. NCSS, LLC. Kaysville, Utah, USA; ncss.com/software/pass).

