The choice for the primary outcome to be a dichotomous measure of glucose-lowering medication use was made in an effort to select a clinically relevant outcome. Participants that are recruited for this study are expected to have wide variability in prescribed types and doses of glucose-lowering medications. Therefore, determining a clinically meaningful dose reduction that would apply to all possible medication scenarios is not feasible. However, if a T2D treatment is able to eliminate the need for glucose-lowering medications entirely, in the absence of significant worsening in glycemia, there is no doubt it can be considered clinically relevant. The secondary outcomes of A1C and fasting glucose will test whether the very low carbohydrate and calorie-restricted dietary approach can benefit glucose control, and secondary anthropometric outcomes (weight, waist circumference, and body fat percentage) will also support the primary outcome, as substantial weight loss in patients with T2D is associated with T2D remission [12]. With careful documentation of glucose-lowering medication use and measures of glucose control, it will also be possible to report on exploratory outcomes of short-term T2D “reversal” using various definitions that have been suggested in the literature, including (1) no glucose-lowering medications, A1C below diabetes mellitus threshold; (2) no glucose-lowering medications, A1C and fasting glucose below diabetes mellitus thresholds; (3) no glucose-lowering medications, A1C and/or fasting glucose in the true normoglycemic range; and (4) A1C below diabetes mellitus threshold and taking only metformin [14, 31]. Though sex will be included as a fixed effect in the logistic regression and linear mixed effects models, a limitation of this study is the inability to determine gender differences in the effectiveness of the intervention. Finally, while a novel aspect of this study is combination of the independently successful strategies of calorie-restriction and low-carbohydrate approach to treating T2D, a limitation of this design is the inability to separate the effects of the two strategies.

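### The two percentage dose-reduction outcomes are assigned to a constrained-baseline mixed model, but a percentage reduction is 0 for everyone at baseline

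*Protocol article*

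**What the plan says.** The Secondary outcomes section of the protocol article lists "Percentage dose reduction in glucose-lowering medications (change in daily dose" and "Percentage dose reduction in blood pressure-lowering medications (change in daily dose" (each closing its parenthesis there). Both are percentage reductions, which can only be measured against the participant's own starting dose.

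The Statistical analysis section gives one method for all secondary measures: "medication dose changes, quality of life, and all blood measures will be analyzed using constrained baseline longitudinal data analysis via a linear mixed model". It justifies the choice by its treatment of missing data, including missing baseline data, because "baseline values are part of the response vector in this model". The only provision for a poor fit is this: "Model specification will be examined by visual inspection of residuals plots, with appropriate data transformations used if indicated". The reporting scale is fixed too: "Secondary continuous outcomes will be reported as mean differences with 95% confidence intervals". The dose outcomes get no method of their own.

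The Inclusion criteria require at least one glucose-lowering drug. Neither the inclusion nor the exclusion criteria require a blood pressure-lowering drug.

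**The concern.** Constrained baseline analysis uses the baseline measurement as an outcome with its own variance, correlated with follow-up. The arms share one baseline mean, and the correlation provides the baseline adjustment and carries information for participants with missing values. An outcome already expressed as change from baseline has no such measurement to offer.

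The first study objective is to reduce and/or eliminate glucose-lowering medication. The binary primary outcome covers elimination. Among the listed outcomes, only the glucose-lowering dose outcome covers reduction. An interval that is too narrow there would go straight into the trial's account of its first objective.

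**Working it through.** **The plan's only design figure.** This is the sample size for the primary outcome, and the present point does not depend on it. With 80% against 60%, two-sided 0.05 and 80% power, the pooled formula gives [1.96·√(2·0.7·0.3) + 0.842·√(0.8·0.2 + 0.6·0.4)]² / 0.2² ≈ 81.2, so 82 per arm, and 82/0.8 = 102.5, so 103. The unpooled formula gives 79, and 79/0.8 = 98.75, so 99. The stated 100 per group is reproduced to within 3%. Below I use 100 × 0.8 = 80 completers per arm ("randomized in a 1:1 allocation ratio").

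**Step 1: the baseline response.** Let d0 and d12 be a participant's dose at baseline and week 12. Percentage reduction is 100·(d0 − d)/d0. At baseline d = d0, so the value is 0 for everyone. Hence Var(baseline) = 0 and Cov(baseline, week 12) = 0. An absolute change in dose, d0 − d, has the same property.

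**Step 2: the covariance matrix.** With week-12 variance s², the 2×2 matrix is [[0, 0], [0, s²]], with determinant 0. An unstructured covariance is singular. If week-12 variance is estimated on its own, what is left is a plain comparison of week-12 means, to which baseline adds nothing.

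**Step 3: one residual variance pooled over visits.** With 160 completers there are 320 responses and 3 fixed effects (intercept, time, arm at week 12). The 160 baseline responses have zero residual. The pooled variance is 158·s²/317 ≈ 0.498·s², so the standard error is √0.498 ≈ 0.71 of its correct value. Type I error of a nominal 5% test is 2·[1 − Φ(1.96/√2)] = 16.6%.

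Take an assumed week-12 SD of 40 points (the type I error does not depend on it):

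| Quantity | Value |
|---|---|
| Correct SE, 40·√(2/80) | 6.32 |
| SE the model reports, (40/√2)·√(2/80) | 4.47 |
| Simulated type I error, random-intercept variance at 0 (5,000 runs) | 17.3% |
| Fitted random-intercept model (400 runs) | 12.8%; mean SE 4.44, empirical SD 5.72 |

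The 400-run figure has a Monte Carlo standard error of √(0.166·0.834/400) ≈ 1.9 points, so it lies about two such errors below 16.6%. Because the covariance is zero, the fitted intercept variance goes to its boundary and the analytic value should apply. A longer repeat of the same fit (831 runs) gave 17.1%, with mean SE 4.45 and empirical SD 6.28.

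**Step 4: dose level as the response.** The simulation assumed between- and within-participant SDs of 28 each, so the total variance is 1,568 and the correlation 0.5. The correct SE is √(0.75·1,568·2/80) = 5.42. The model's mean SE was 5.42, and the empirical SD over 400 runs was 5.68. The model is sound once the baseline varies.

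**Step 5: missing values and the denominator.** Without d0 the percentage cannot be computed at all, so putting baseline in the response vector recovers nothing. If week 12 is missing, a baseline of 0 says nothing about it. If d0 = 0, the percentage is 0/0, or −d12/0 when a drug is started. For blood pressure drugs this concerns everyone taking none at entry. The protocol does not give that share. If it were 20% to 40%, purely as an assumption, 40 to 80 of 200 participants would have no value.

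**The case against.** The best reply is that the authors meant dose level. Both outcomes carry the gloss on change in daily dose, the analysis section speaks of dose changes, and in this model class the response is normally the level, with change as the estimated contrast. Weight reduction in kilograms is listed in the same shorthand, and nobody would model it as zeros at baseline. Part of this stands: with dose level as the response the model works. It does not rescue the text. Weight has one unit, and its level model returns kilograms. A level model for dose does not return a percentage reduction, and raw doses of different drugs share no unit. The stated fallback does not help, since no transformation gives a constant any variance.

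It is also fair that a condensed article may leave to fuller documents how drugs are combined and how new ones count. Silence on those details is not the point here. The mismatch between the named outcome and the named model is in the text itself.

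Stronger readings that a reader might infer are not supported:

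- That the model cannot be fitted. Some covariance structures do fit, and the protocol names none. The trouble is then the standard error.
- That the glucose-lowering percentage is also undefined for some participants. Every participant enters on at least one such drug. The difficulty arises only if the percentage is taken drug by drug and a new drug is added, which the protocol does not say.
- That drug starts in usual care will be silently dropped. For glucose-lowering drugs this rests on the same drug-by-drug reading. The protocol states no expectation about starts of blood pressure drugs.
- That the Discussion concedes there is no single daily dose. Its remark that "determining a clinically meaningful dose reduction that would apply to all possible medication scenarios is not feasible" concerns a threshold of clinical relevance, given as the reason for a binary primary outcome.

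**Conclusion.** The concern holds for both dose outcomes as named and the model as assigned. Baseline carries no information, and the stated advantage for missing baseline data is not available. Depending on the covariance structure, the fit is singular, reduces to a week-12 comparison, or understates the standard error by a factor of about √2, with type I error near 17% instead of 5%. That last figure assumes the literal reading, a residual variance common to both visits and a normal week-12 outcome; it is not a prediction of what the trial team will run. The undefined percentage is in practice a problem of the blood pressure outcome, and its extent is unknown. Only secondary outcomes are affected. The primary logistic regression is not. The plan should be corrected, but nothing in the design has to change.

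**What to change.** Preferred: put dose level in the response vector at baseline and week 12, on one scale per drug class. One such scale is the sum, over all drugs in the class, of daily dose divided by a fixed analytic reference dose for that drug, with zeros allowed and newly started drugs counted. The reference doses serve only as units for analysis and have no bearing on treatment. Report the week-12 difference between arms with its 95% confidence interval, and give percentage change descriptively. Participants with no baseline blood pressure drug then stay in the analysis.

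Alternative: keep the percentage, but analyse its week-12 value as a single response among those with a baseline dose, using a suitable method such as ANCOVA or a rank-based analysis. Say how those without a baseline dose are handled.

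The cost is small: a change of wording, a reference-dose table, and an index that is less direct to read than a percentage. It needs daily dose by drug at both visits in both arms. The article mentions medications at baseline and medication usage at the Pharm-TCR visits. It does not list medication among the final-visit measures for usual care, so confirm that dose is captured there.

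### The secondary mixed models name site and sex but not the medication stratum used in randomisation, so standard errors are conservative for outcomes that stratum predicts beyond baseline

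*Protocol article*

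**What the plan says.** Methods/design sets out the randomisation: "Participants will be stratified by site (pharmacy) and glucose-lowering medications (two or fewer, three or more (or taking exogenous insulin" being the second category. Patients are "randomized in a 1:1 allocation ratio using permuted block sizes", and they "will be recruited from across 12 pharmacy locations in the province of British Columbia, Canada".

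Under Statistical analysis, the primary logistic model is specified "with the stratified allocation factors included as fixed effects together with trial arm and sex". Site and medication stratum are therefore both in the primary analysis.

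For the secondary outcomes (body measurements, blood tests, blood pressure, changes in dose and quality of life) the same section says that the data "will be analyzed using constrained baseline longitudinal data analysis via a linear mixed model". In that model "baseline values are part of the response vector in this model", so the comparison between arms is in effect adjusted for baseline. One further term is given there: "study site will be included as a random effect in the linear mixed models to account for site variability in the outcome measures". The Discussion supplies another: "Though sex will be included as a fixed effect in the logistic regression and linear mixed effects models".

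The medication stratum is not mentioned for the mixed models. No reason is given for the difference from the primary model.

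**The concern.** Stratified allocation makes the arms similar in medication burden. The estimated difference between arms therefore varies less from trial to trial than under simple randomisation. A model without the stratum does not know this: it counts the variance due to the stratum as residual noise and reports a standard error that is too large. The test becomes conservative and the interval wider than it need be.

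The article carries one stratification factor (site) into the secondary models and does not name the other. An analyst following the text would fit site and sex only. What is at stake is precision on the secondary outcomes. Some of these matter for interpretation, because the Discussion relies on A1C and fasting glucose to show that stopping drugs does not come at the cost of glycaemic control.

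**Working it through.** **The plan's own figure.** The only sample-size figure concerns the primary outcome, and this point does not depend on it. It does reproduce. For 80% vs 60%, two-sided 0.05 and 80% power, the pooled formula is n = [1.96·√(2·0.7·0.3) + 0.8416·√(0.16 + 0.24)]² / 0.2² = 81.2, so 82 per group, and 82/0.8 gives 103. The unpooled formula gives 79, or 99 after attrition. The stated 100 lies between them.

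**Inputs from the article.** N = 200; 12 sites × 2 medication strata = 24 cells, or 200/24 ≈ 8.3 patients per cell; 1:1 permuted blocks; baseline in the response vector; site random; sex fixed.

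**Assumptions, not in the article.** Half of patients in each stratum (p = 0.5); baseline to week-12 correlation 0.6; blocks of 4; site SD 0.2; a range of stratum effects that includes zero.

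**Formula.** Let D be the stratum's shift in the week-12 value, in residual SD units, after baseline, site and sex. If the stratum is balanced by design and left out:

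- model SE / true SE: r = √(1 + p(1−p)D²)
- actual type I error = 2[1 − Φ(1.96·r)]

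| D | Excess SE | Type I error |
|---|---|---|
| 0 | 0% | 0.050 |
| 0.2 | 0.5% | 0.049 |
| 0.4 | 2.0% | 0.046 |
| 0.6 | 4.4% | 0.041 |
| 0.8 | 7.7% | 0.035 |
| 1.0 | 11.8% | 0.028 |

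For example, D = 1 gives √(1 + 0.25) = 1.118.

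**Simulation.** There were 3000 runs per scenario with all 200 patients observed. A baseline-adjusted linear model with site as fixed effects stood in for the constrained mixed model. Shifts are in within-stratum SD units.

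| Shift at baseline | Shift at week 12 | Mean SE, stratum omitted | Mean SE, included | Excess | Type I error, omitted | Type I error, included |
|---|---|---|---|---|---|---|
| 0 | 0 | 0.1141 | 0.1142 | none | 0.040 | 0.041 |
| 0.8 | 0.5 | 0.1138 | 0.1139 | none | 0.050 | 0.051 |
| 0.5 | 0.5 | 0.1149 | 0.1141 | 0.7% | 0.050 | 0.053 |
| 1.0 | 1.0 | 0.1167 | 0.1140 | 2.4% | 0.048 | 0.049 |
| 0.5 | 1.0 | 0.1239 | 0.1140 | 8.7% | 0.043 | 0.056 |
| 0 | 0.8 | 0.1276 | 0.1139 | 12.0% | 0.030 | 0.051 |

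Monte Carlo error on each rate is about √(0.05·0.95/3000) = 0.004. Small departures from 0.05 should not be read as real.

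The two approaches agree. In the last row the residual SD after baseline is √(1 − 0.6²) = 0.8, so a shift of 0.8 is D = 1, and the formula gives 11.8% against the simulated 12.0%. When the stratum shifts baseline and week 12 alike, baseline absorbs most of it and the excess is 2.4% or less.

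**Which outcomes could be at the upper end.** A percentage dose reduction is zero at baseline by construction. If it is analysed as listed under Secondary outcomes, baseline adjustment absorbs nothing, and the stratum is itself a measure of baseline medication burden. For A1C and fasting glucose there is a weaker argument. The Pharm-TCR intervention section individualises care plans on baseline medication use, and gives patients above an insulin threshold a modified meal plan. All of those patients fall in the higher stratum, so it could predict change as well as starting level.

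**The case against.** The strongest reply is that the omission is inferred from silence. The Statistical analysis section does not mention sex for the mixed models either; that term appears only in a limitation in the Discussion. The section is therefore not a closed list, the article is a condensed account, and nothing says that the stratum is excluded. This stands as a limit on how firmly the omission can be asserted. It does not remove the point: the article does name covariates for these models, including one of the two stratification factors, and as written they do not match the randomisation.

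A reader might go further and infer that the standard errors of all secondary outcomes are too wide. The article does not support that. Baseline is already in the model, nothing is stated about how strongly the stratum predicts any outcome, and there is no particular reason to expect residual prediction for weight, waist, lipids, liver enzymes, blood pressure or quality of life.

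A reader might also equate the omission with discarding patients. That overstates it. Stratified allocation has already balanced the factor, so the estimate itself loses little. In the 12% scenario the empirical SD of the estimate was 0.1162 with the stratum omitted and 0.1147 with it included. It is mainly the reported standard error that is too large.

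Nor is it an error in itself that the primary and secondary models contain different factors. In a linear model, adding a balanced covariate does not change the mean difference being estimated.

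**Conclusion.** The point holds in a conditional form. As described, the secondary mixed models contain site and sex but not the medication stratum, which is both a randomisation factor and a term in the primary model. If they are fitted that way, model-based standard errors are conservative for outcomes that the stratum predicts beyond baseline. The excess is about 0 to 2% where baseline carries the information, and about 12% (type I error near 0.03) where the stratum strongly predicts change.

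These sizes rest on the assumed stratum split, correlation, block size and stratum effects; the article gives none of them. The treatment effect is not biased, type I error is not inflated, the primary analysis is not affected, and no power is claimed for the secondary outcomes. This is an inexpensive gain in precision and consistency, not a threat to validity.

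**What to change.** State that every secondary mixed model includes the medication stratum and its interaction with visit as fixed effects, alongside the site random effect and sex. The interaction is needed because a main effect alone forces the same shift at baseline and week 12, and so cannot capture a stratum that predicts change. If a fuller analysis plan already includes these terms, it is enough to say so.

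The cost is one line of specification and, with two visits, two fixed-effect parameters. Where the stratum predicts nothing, almost nothing is lost: the simulated standard error was 0.1142 with it and 0.1141 without.

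### The stated 80% power removes dropouts from both arms, but the primary analysis keeps Pharm-TCR dropouts as failures; if the 60% is a completer rate, power for the planning effect is about 44–50%

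*Protocol article*

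**What the plan says.** All the relevant statements are in the Statistical analysis section of the protocol article.

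- **Planning rates.** The article says "the sample size was calculated based on an expected proportion of medication use of 80% in the TAU group", with "a 20% difference in the proportion of participants on glucose-lowering medications at 12 weeks in the Pharm-TCR group". Read as an absolute difference, this is 80% against 60% on medication.
- **Power claim.** "A sample size of 100 per group provides 80% power to detect a 20% difference in the proportion of patients on glucose-lowering medications", and this is "accounting for 20% attrition with a two-sided *P* value of 0.05".
- **Endpoint and model.** The primary outcome is "using or not using glucose-lowering medication at 12 weeks - and data will be analyzed by logistic regression".
- **Dropout rule.** Participants who do not complete the intervention, or who are "lost to follow up from the Pharm-TCR group will be retained in the analyses and will be considered as not achieving the primary outcome". No corresponding rule is given for TAU losses.
- **Margin in the TAU rate.** The authors expect no TAU participant to stop medication and describe the 80% as a conservative choice.

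Allocation is 1:1 (Methods/design).

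**The concern.** The power sentence and the dropout rule treat the same patients differently. An allowance for attrition treats dropouts as lost sample: fewer patients are analysed and the difference between arms is unchanged. The dropout rule keeps those patients in the Pharm-TCR denominator and scores them as failures. In that arm attrition then costs no patients, but it moves the rate towards the control rate and shrinks the difference.

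The power statement is the only statistical justification given for N = 200. If it was computed for an analysis other than the one specified, a reader of a null result would wrongly take the trial to have had 80% power for the stated effect.

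**Working it through.** **Inputs.** Two-sided alpha 0.05; 100 per arm; 80% on medication in TAU; 60% in Pharm-TCR; 20% attrition; Pharm-TCR dropouts counted as failures. All are from the Statistical analysis section. I take a failure to mean still on medication, and assume attrition is 20% in each arm.

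**Formulae.** With d = p1 − p2:

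- pooled: power = Φ((d − 1.96·SE0)/SE1)
- unpooled: power = Φ(d/SE1 − 1.96)

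SE0 is the standard error using the pooled proportion, and SE1 uses the separate proportions.

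**Step 1: reproduce the stated 80%.** Remove 20% from each arm, leaving 80 against 80, at 0.80 against 0.60.

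- SE0 = √(0.70 × 0.30 × 2/80) = 0.0725
- SE1 = √(0.16/80 + 0.24/80) = 0.0707
- pooled: Φ((0.20 − 0.1420)/0.0707) = Φ(0.82) = 79.4%
- unpooled: Φ(0.20/0.0707 − 1.96) = Φ(0.87) = 80.7%

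Exact enumeration of the chi-square test gives 80.1%. The stated figure therefore matches deletion of dropouts from both arms with the full 20-point difference retained. A relative reading of the 20% (0.80 against 0.64) gives only about 62% at 80 per arm, so the absolute reading is the one used.

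**Step 2: apply the written dropout rule, taking 60% as the completer rate.**

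- Pharm-TCR rate = 0.20 + 0.80 × 0.60 = 0.68
- difference = 0.80 − 0.68 = 0.12

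**Step 3: take 60% as the rate in all randomised patients, with dropouts already counted as failures.** The difference stays at 20 points and all 100 Pharm-TCR patients are analysed. The implied completer rate is (0.60 − 0.20)/0.80 = 0.50.

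| Scenario | TAU: n, rate | Pharm-TCR: n, rate | Power, pooled / unpooled |
|---|---|---|---|
| Stated calculation | 80, 80% | 80, 60% | 79.4% / 80.7% |
| 60% among completers, TAU losses excluded | 80, 80% | 100, 68% | 43.8% / 45.9% |
| 60% among completers, all TAU analysed | 100, 80% | 100, 68% | 49.0% / 49.7% |
| 60% among all randomised, TAU losses excluded | 80, 80% | 100, 60% | 83.2% / 85.4% |
| 60% among all randomised, all TAU analysed | 100, 80% | 100, 60% | 87.6% / 88.5% |

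Exact enumeration for the second and third rows gives 44.1% and 49.0%.

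**Step 4: sensitivity to attrition.** With 60% among completers, pooled power from TAU losses excluded to all TAU analysed is 69–72% at 10% attrition, 57–61% at 15% and 32–37% at 25%.

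**Step 5: sensitivity to the TAU rate.** Ranges run from 80 TAU patients (pooled) to 100 (unpooled).

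- Pharm-TCR held at 68%: TAU at 85% gives 76–82%; TAU at 90% gives 96–98%; TAU near 100% gives above 99%.
- The 20-point completer difference kept and then diluted: TAU 90% against 0.20 + 0.80 × 0.70 = 76% gives 69–77%; 95% against 80% gives 86–91%; nearly 100% against 84% gives 98–99%.

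None of these calculations reflects the covariates in the logistic model.

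**The case against.** The strongest reply has three parts.

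**The text does not say that the 60% is a completer rate.** The section opens by committing to intention to treat and describes the difference at group level. A 60% that already includes dropouts fits those words, and power is then 83–89%, above the claim. This stands. The completer reading is inferred from the fact that 80 per arm with an undiluted difference reproduces the 80%. A reader might conclude that the design misses 80% on any reading; the document does not support that. On the group-level reading, what remains is that an allowance removing 20 patients from Pharm-TCR does not describe the analysis. An allowance may still be needed for TAU, because the rule does not cover losses there.

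**The 80% TAU rate is deliberately pessimistic.** This also stands. The authors expect essentially no TAU patient to stop, and step 5 shows high power after dilution when TAU use is near 100%. A reader might infer that the trial has roughly an even chance of success. That holds only at the 80% TAU rate with a 60% completer rate, and the authors do not present 80% as their expectation.

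**The stated figure is not a wrong sum.** Correct: it reproduces. The fault is a mismatch between two statements, not an arithmetic slip.

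Two other replies carry less weight. Leaving the matter to an analysis plan does not help, since the power claim and the dropout rule are both given in this article. And counting dropouts as failures may well be a sound rule; the point is only that the power was not computed under it.

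**Conclusion.** The point holds in a limited form. The 80% power matches an analysis that drops 20% of each arm, and the article specifies a different one.

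- If the 20-point difference is among completers, power for the stated planning effect is about 44–46% with TAU losses excluded, or 49–50% with all 100 TAU patients analysed.
- If the difference already counts dropouts as failures, power is about 83–85% or 88–89%. The claim is met, but the attrition allowance does not match the analysis.

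The article does not say which is meant; its calculation points to the first. The figures assume 20% attrition in each arm, failure meaning still on medication, and an unadjusted comparison of two proportions. They are conditional on the 80% TAU rate and should not be read as the trial's likely power.

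**What to change.** N, endpoint and model can stay as they are. In the sample size paragraph:

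1. State whether the 20-point difference is before or after Pharm-TCR dropouts are counted as failures.
2. Restate the power under the dropout rule actually used, saying how TAU losses enter the calculation. Under the rule as written, the figures are those in the verdict.

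If the sponsor also chooses to count TAU losses as still on medication, that changes the written rule and should be presented as a change. TAU then becomes 0.20 + 0.80 × 0.80 = 84% against 68%, with 100 per arm, and power is about 76–77% (75.9% pooled, 76.9% unpooled).

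The cost is one corrected sentence and a re-run of the power calculation, with a possibly less favourable stated power. Showing power at a higher TAU rate beside it would let readers see the margin that the conservative 80% provides.
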